### Data analyses

TAIPAN will undertake four separate analyses to address the study aims (Table 2).

TAIPAN’s primary aim will be addressed by examining the temporal relationship between community prevalence of viraemia and incidence of HIV infection in gay and bisexual men. For each year of follow up, the community prevalence of HIV viraemia as determined by the calendar year will be entered as an independent variable in the regression. In addition to estimating the effect of community prevalence of viraemia, we will control at the individual level for other demographic, clinical and behavioural determinants of acquisition of new HIV infection, and recent sexual risk practices. We will use random effects Poisson models to undertake multi-level analyses that will allow us to include group-related variables (community prevalence of viraemia), individual variables (demographic, clinical, and behavioural) and time.

The study period will be divided into three-year periods defined by treatment guidelines and policy. The first period will encompass 2009–2011 and serve as a ‘before’ treatment as prevention period. The second period will encompass 2012–2014 and represent a transition period given that several Australian jurisdictions began to expand treatment as prevention initiatives during this time. And the third period will encompass 2015–2017, representing the full implementation of treatment as prevention given that early ART initiation was recommended for both individual and public health purposes. In regards to time lags, we assume that HIV incidence is affected by the estimated prevalence of virological suppression from the preceding year.

The second analysis will examine the temporal relationship between the three time periods described above and the incidence of treatment initiation among men newly diagnosed with HIV (Secondary Aim 1). Using the study periods described above in a regression analysis, incidence of treatment initiation among men newly diagnosed with HIV will be the outcome variable while controlling for clinical, demographic and behavioural factors. Given its historical role in determining when to initiate treatment, CD4 cell count at diagnosis and HIV viral load will also be included in the multivariate model.

The third analysis will determine incidence and predictors of repeat HIV testing (Secondary Aim 2). To calculate annual estimates we will allocate follow-up time and the incident of repeat testing (i.e., the point at which a second test is achieved) to the calendar year in which it occurs. With this approach it is possible that a patient might achieve multiple incidents of repeat testing in one calendar year. In addition to evaluating changes in the incidence of repeat HIV testing over time, this analysis will employ a regression analysis to identify demographic, behavioural and clinical factors associated with repeat testing incidence among gay and bisexual men in the negative cohort.

The fourth analysis will estimate the incidence of viral suppression among those newly diagnosed and predictors of incidence of viral suppression among the positive cohort (Secondary Aim 3). This analysis will employ Cox proportional hazards regression. Further, we will estimate the median time from diagnosis to first viral suppression by calendar year among those who are diagnosed during the study period, stratified by CD4 cell count at diagnosis. For this analysis and all others, statistical significance will be set at *p* < 0.05.

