## Methods

### Study design

This study will involve a longitudinal cohort design using de-identified, electronic medical records extracted for the period 1 January 2009 to 31 December 2017.

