The community prevalence of viraemia is defined as the proportion of gay and bisexual men (diagnosed and undiagnosed) with a viral load of ≥200 RNA copies/mm^3^. A viral load of ≥200 was selected as this is a commonly-used clinical marker of viral suppression and a recent meta-analysis found no transmission of HIV among individuals with less than 200 RNA copies/mm^3^ [14]. Community prevalence of viraemia was selected as it has been demonstrated to have the strongest correlation with HIV incidence over other measures (e.g., mean viral, treatment coverage) [15]. Our measure of viraemia will comprise the following four components:Annual prevalence of viraemia: will be calculated within the positive cohort using the annual prevalence of viral load test results of ≥200 RNA copies/mm^3^ (‘viraemia’) at each patients last viral load test within a calendar year. We will conduct sensitivity analyses to include any viral load test ≥200 RNA copies/mm^3^ in a year and also using a higher threshold of ≥1000 RNA copies/mm^3^.Annual prevalence of diagnosed HIV infection among gay and bisexual men: will be estimated using population prevalence techniques developed by and used for Australia’s national HIV surveillance [6]. This approach produces a prevalence estimate using data on HIV diagnoses from Australia’s National HIV Registry, adjusting for duplicate entries, deaths, and migration outside of Australia. For this estimate we will focus on HIV diagnoses where homosexual contact is identified as the route of transmission.Annual prevalence of undiagnosed HIV infection among gay and bisexual men: will be estimated using standard back-project models [16] and validated against a separate bio-behavioural survey conducted in 2013–2014 and to be repeated in 2017 [17].Prevalence of viraemia in gay and bisexual men with undiagnosed HIV infection: will be calculated using an estimate of undiagnosed infection obtained from the back-projection models coupled with the assumption that all undiagnosed men have viral loads of ≥200 RNA copies/mm^3^. We will also consider different viral load levels among undiagnosed men by using data from the National HIV Registry and stratifying viral load at diagnosis by HIV testing history (i.e., reported time since HIV test prior to diagnosis).

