## Discussion

Although treatment as prevention has already been shown to be highly effective among serodiscordant couples, further evidence is required to determine its community-level impact on HIV incidence among gay and bisexual men. This issue is particularly relevant in the Australian context, where testing and treatment coverage is high but where there has been no decline in annual HIV diagnoses [6]. The two large cohorts established in this study will provide detailed information on the level of testing and treatment coverage that can be achieved and, in the turn, the impact on HIV incidence.

While clinical trial results and modelling studies have fostered optimism about the treatment as prevention’s public health potential, the ultimate reduction of incidence may be somewhat less than expected in gay and bisexual men [26]. In Australia, an estimated 12% of people living with HIV are undiagnosed [6] with the average time between infection and diagnosis estimated to be between two and three years [22]. Undiagnosed infections contribute disproportionately to HIV transmission due to higher viral loads and sexual practices [5]. It is, therefore, a key strength of this study that it will consider the roles of diagnosed and undiagnosed HIV in onward transmission among gay and bisexual men.

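### The annual viraemia series is partly modelled and assumed, but the primary regression as described uses it without carrying its uncertainty, so the interval is likely too narrow and the coefficient may be biased

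*Protocol article*

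**What the plan says.** The primary model is set out under Data analyses: "We will use random effects Poisson models to undertake multi-level analyses". It holds the group-level viraemia variable, "individual variables (demographic, clinical, and behavioural) and time". For each year of follow-up, "the community prevalence of HIV viraemia as determined by the calendar year will be entered as an independent variable in the regression". A one-year lag applies: "we assume that HIV incidence is affected by the estimated prevalence of virological suppression from the preceding year". Records are "extracted for the period 1 January 2009 to 31 December 2017" (Study design), so at most eight viraemia values are usable: 2009-2016 set against incidence in 2010-2017.

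Outcome 1 under Study outcomes builds the annual value from four parts:

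- Viraemia in diagnosed men is measured: it "will be calculated within the positive cohort using the annual prevalence of viral load test results", taking each man's last test of the year.
- Diagnosed prevalence is an estimate from national registry data, corrected for duplicates, deaths and migration.
- Undiagnosed prevalence "will be estimated using standard back-project models [16] and validated against a separate bio-behavioural survey" run in 2013-2014 and again in 2017.
- Viraemia in undiagnosed men is set at 100%, with alternative levels to be considered.

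The planned sensitivity analyses on this exposure change which test counts, the viral load threshold and the viral load assumed for undiagnosed men. None varies the back-projected number of undiagnosed men.

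**The concern.** A regression that takes its covariate at face value reports only the sampling error of the outcome. Here one component of the covariate is a back-projection and another is an assumption, and their error has no described route into the standard error of the viraemia coefficient. That coefficient is the answer to the primary aim.

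Two features sharpen the problem. First, time is in the model. If viraemia falls steadily, most of its variation is absorbed by time, and the coefficient rests on small departures from trend that may be no larger than the error in the series. Second, the modelled part may weigh more, and be less well determined, towards the end of the series. The Discussion gives "the average time between infection and diagnosis estimated to be between two and three years", so many recent infections would not yet have appeared as diagnoses.

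At stake is an overstated precision for the primary result and, depending on how the errors behave, a real association that is weakened or one that is exaggerated. This is a separate matter from there being only eight annual values.

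**Working it through.** **The plan's own figure.** The only stated figure for the primary aim is 80% power for a hazard ratio of 0.80 with 336 cases a year. Comparing adjacent years with 336 and 0.80 × 336 ≈ 269 cases gives about 605 events. Power = Φ(|ln 0.80| × √(605/4) − 1.96) = Φ(0.223 × 12.3 − 1.96) ≈ 78%. The figure reproduces. It does not involve the viraemia series, so it does not bear on this point.

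**How much of the exposure is back-projected.** Inputs: 12% of people with HIV undiagnosed (Discussion) and 73% of diagnosed people on treatment in 2014 (Background). Both are national figures for all people with HIV. Suppression on treatment is assumed. Share = 0.12 / [0.12 + 0.88 × (1 − coverage × suppression)].

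- 73% coverage, 90% suppressed: 0.12 / (0.12 + 0.302) = 28%.
- 73%, 100%: 0.12 / (0.12 + 0.238) = 34%.
- 85%, 95% (assumed later level): 0.12 / (0.12 + 0.169) ≈ 41-42%.
- 95%, 95% (assumed later level): 0.12 / (0.12 + 0.086) = 58%.

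The share grows as suppression rises, provided the undiagnosed share stays at 12%.

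**How complete the last exposure year is.** Assume infections spread evenly over 2016, an exponential delay of mean m years, and a data cut on 31 December 2017. The share still undiagnosed is m × (e^(−1/m) − e^(−2/m)): 48%, 55% and 61% for m = 2, 2.5 and 3. This is the share of one year's infections, not the error in the total undiagnosed count. It supports the idea that late values are less certain but does not measure by how much.

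**Effect on the coefficient and its interval.** The documents give neither an annual series nor an error size, so the following is illustrative. Assumed viraemia among men with HIV over the eight lagged years: 0.514, 0.498, 0.474, 0.449, 0.425, 0.409, 0.352, 0.304. Undiagnosed men contribute 0.12 throughout (23% of the first value, 39% of the last). Error enters only that part. Incident cases average 420 a year, the true log-log slope is 1, and a plain Poisson model is fitted with a 95% Wald interval, 3,000 runs per scenario. Linear time explains 92% of the variation in log viraemia, which leaves a residual SD of 0.054.

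| Error in the undiagnosed part | Mean slope, coverage: time in model | Mean slope, coverage: no time |
|---|---|---|
| None | 1.00, 96% | 1.00, 95% |
| Independent, 5% | 0.95, 94% | 1.00, 93% |
| Independent, 10% | 0.83, 88% | 0.98, 91% |
| Independent, 20% | 0.48, 49% | 0.93, 74% |
| Independent, 10% growing threefold | 0.58, 63% | 0.97, 74% |
| Smooth (ρ = 0.9), 10% | 0.99, 94% | 1.00, 91% |
| Smooth, 20% | 0.95, 89% | 1.01, 77% |
| Smooth, 10% growing threefold | 1.00, 87% | 1.04, 70% |
| Systematic, reaching −30% in last year | 0.66, 74% | 0.81, 42% |
| Systematic, reaching +30% in last year | 1.63, 85% | 1.26, 55% |
| Linked to same year's diagnoses | 1.05-1.12, 97-99% | 1.01, 97-100% |

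A hand check on the independent-error rows uses the classical factor σ²(residual) / [σ²(residual) + σ²(error)]. A 10% error in a part that makes up about 0.29 of the total gives an error SD near 0.029, so 0.054² / (0.054² + 0.029²) ≈ 0.78. At 20% it is 0.054² / (0.054² + 0.058²) ≈ 0.46. The simulated 0.83 and 0.48 are close to these.

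**The case against.** The strongest reply is that the article says how viraemia enters the model, not that it is treated as exact. Variance estimation is the kind of detail a condensed article leaves to an analysis plan, and none is shown. This stands as a limit: the article does not prove that propagation is unplanned. What can be said is that the described model, read as written, has no place for this error, and the listed sensitivity analyses and surveys do not supply one.

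Three stronger readings are tempting, and the documents do not support them.

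- A reader might infer that the coefficient must be biased towards zero. That needs error that is roughly independent from year to year, with time in the model. Back-projection error may well be smooth. Smooth error leaves the mean slope near 1, late systematic error can inflate it, and error shared with the same year's diagnoses gave slopes slightly above 1 with no under-coverage.
- A reader might infer that the whole exposure is modelled. It is not: viraemia in diagnosed men is measured, in a cohort meant to hold about 90% of HIV-positive gay and bisexual men in both states.
- A reader might take it as established that the last years are the least certain. The delay to diagnosis suggests this, but no section says so, no data cut for the back-projection is stated, and the 2017 survey is a check at that end of the series.

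It is also fair that the size is assumed. With a constant 10% error and other assumed series, coverage was 92-95%, which is minor. The planned model has random effects whose level is not stated. Allowing for extra year-level variation restored coverage in some checks (95-100%) but not in others (64-99%), so it cannot be relied on.

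**Conclusion.** The point holds in a limited form. A covariate that is part measured, part estimated and part assumed enters the primary regression with no described allowance for its uncertainty. The modelled part is material: about 28-34% of viraemic men on the documents' figures with 90-100% suppression on treatment, and more later if the undiagnosed share does not fall.

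The interval is likely to be too narrow under most error structures tried. Across several assumed series with 10-30% error in the undiagnosed part, Poisson coverage ran from about 52% to 95%; the scenarios tabulated above reach slightly lower. The exception is error tied to the same year's diagnoses. The direction of bias in the coefficient is open: attenuation under independent error with time in the model, little change under smooth error, and either direction under late systematic error.

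All sizes rest on an assumed series and assumed error variances. The documents support the mechanism, not a particular magnitude.

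**What to change.** Keep the planned Poisson model and report a second analysis beside it. Draw the whole annual viraemia series jointly from the bootstrap or posterior distributions of its components (viraemia in diagnosed men, diagnosed prevalence, undiagnosed count, viraemia in undiagnosed men), keeping the correlation between years, and fit the incidence model with that error included. A joint measurement-error model is preferable: simply refitting over redrawn series widens the interval but does not undo attenuation.

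Add a sensitivity analysis that varies the back-projected count in the last exposure years over a stated plausible range, upwards and downwards. Do not drop those years: the 2015 and 2016 exposures feed incidence in 2016 and 2017, two of the three years of the full-implementation period. State the data cut for the back-projection, and report the annual series with its intervals.

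The cost is more analysis work and a wider, less favourable interval. No new data are needed.

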### Sample size

Sample size calculations are based on the estimated number of gay and bisexual men diagnosed with HIV annually in New South Wales and Victoria, [6] and assuming a modelling-derived 30% reduction in infections to 420 per year in 2015–2017 (i.e., following the full implementation of treatment as prevention) [22]. For HIV incidence (Primary Aim) an estimated 80% of men diagnosed annually will have some HIV testing history, [23, 24] which equates to 336 incident cases annually and will provide 80% power to detect annual declines in the incidence rate of at least 20% (hazard ratio [HR] = 0.80). Regarding treatment initiation (Secondary Aim 1), assuming a rate of treatment initiation of 36 per 100 person years (unpublished data from Australian HIV Observational Database) and an estimated 420 men newly diagnosed per year, our analysis will have 80% power to detect annual relatives changes in treatment initiation after a new HIV diagnosis of at least 36% (HR = 1.36).

For repeat HIV testing (Secondary Aim 2), it is estimated that 80% of men in the negative cohort will be tested at least once annually for HIV [23, 24] and that 25% will have one further test in the year [25]. If the cohort contains approximately 40,000 men then this translates into 8000 repeat testers annually, which will provide sufficient power to detect at least a 6% annual increase in the incidence of repeat testing (HR = 1.06). And for viral suppression (Secondary Aim 3), if we assume that 90% of newly diagnosed men will start treatment [26] then we will have 80% power to detect a 15% increase in the annual incidence of viral suppression (HR = 1.15). Trend tests over multiple years will have greater power as will combining over multiple years as per the three-year study periods relative to the implementation of treatment as prevention (see Data Analyses).

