### Participants

Using de-identified data extracted from ACCESS sites, two patient cohorts of gay and bisexual men will be established: one comprising HIV positive men (‘positive cohort’) and the other HIV negative men (‘negative cohort’). The positive cohort will consist of approximately 13,000 HIV positive gay and bisexual men (approximately 90% of all gay and bisexual men with HIV in both states) and the negative cohort will consist of at least 40,000 HIV negative gay and bisexual men (approximately half of the population).

Both cohorts will be limited to men aged 16 years and older for whom there is at least once record indicating a history of sexual contact with other men. Indicators of same sex contact can be behavioural (i.e., self-reporting same sex partners), identity-based (i.e., recorded sexual orientation as gay or bisexual), or procedural (i.e., collection of an anal swab for STI testing). The positive cohort will include patients recorded as HIV positive or those who receive an HIV diagnosis during the study period. The negative cohort will include patients whose first record of HIV testing during the study period is negative. If during the course of the study a person is diagnosed with HIV, they will be reclassified to the positive cohort. Follow-up during the study period will be based on records from the participating services as well as the pathology conducted by participating laboratories.

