**Fig. 1 Fig1:**
[figure not shown]
Method for calculating the prevalence of HIV viraemia among diagnosed and undiagnosed gay and bisexual men

#### Outcome 2

HIV incidence will be calculated using repeat testing among the negative cohort, [18] which will consider patients with two or more HIV tests for whom the first test was negative. We expect that more than 80% of gay and bisexual men will have at least two tests over the study period. An incident infection will be defined as an HIV diagnosis following a negative test and time at risk will be calculated as the time between each patient’s first and last test or a patient’s first test and HIV diagnosis. The number of incident infections will be divided by the person time (in years) at risk.

#### Outcome 3

Data from the positive cohort will also be used to calculate the incidence of ART initiation (i.e., the point at which ART is initiated) with the follow-up period defined as the time after HIV diagnosis (person years of infection). This variable will be restricted only to men diagnosed with HIV during the study period.

#### Outcome 4

Data from the negative cohort will be used to calculate the incidence of repeat diagnostic HIV testing. The incident event is defined as the point at which a patient achieves a second HIV test within six weeks to 12 months of a previous test, with follow-up time defined as the period between a patient’s first HIV test and last clinical encounter. Follow-up time will cease if a patient has no recorded service event of any kind within a two year period but will resume at the point of future service events (i.e., reengages with a participating service). Follow-up will also cease if a patient is diagnosed with HIV.

#### Outcome 5

Among the positive cohort, the incidence of viral suppression will be calculated. Viral suppression is defined as two consecutive viral load tests of <200 RNA copies/mm^3^ separated by at least three months; the first test will be taken as the point of suppression for calculating time. This variable will only be calculated among patients with no history of previous treatment and will exclude those for whom there is no or only one viral load test result. We will conduct a sensitivity analysis with a higher viral load threshold of <1000 RNA copies/mm^3^.

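### The primary-aim power rests on 336 cases a year drawn from all diagnoses in both states, but Outcome 2 counts only negative-cohort men with a recorded earlier negative test

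*Protocol article*

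**What the plan says.** The Sample size section of the protocol article says its calculations are "based on the estimated number of gay and bisexual men diagnosed with HIV annually in New South Wales and Victoria", "assuming a modelling-derived 30% reduction in infections to 420 per year in 2015–2017". For the primary aim it then states that "an estimated 80% of men diagnosed annually will have some HIV testing history", "which equates to 336 incident cases annually and will provide 80% power to detect annual declines in the incidence rate of at least 20" per cent (hazard ratio 0.80). No further reduction follows.

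The outcome is defined more narrowly:

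- Under Study outcomes, Outcome 2 calculates incidence by repeat testing within the negative cohort, "which will consider patients with two or more HIV tests for whom the first test was negative".
- Under Participants, the entry rule reads "The negative cohort will include patients whose first record of HIV testing during the study period is negative". Follow-up comes only from records of participating services and laboratories.
- The same section gives the size: "the negative cohort will consist of at least 40,000 HIV negative gay and bisexual men (approximately half of the population". The Discussion repeats the half.

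Two other statements bear on the point. Under Cohorts, the network aims to capture all HIV diagnoses in both states. The Sample size section closes by saying that multi-year trend tests and pooling by three-year period will have more power than the annual comparison, but gives no figure.

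**The concern.** The event count and the estimator refer to different populations. The 336 is a two-state count of diagnosed men who have been tested at some time, anywhere. An Outcome 2 case needs a negative test that is inside the network, inside 2009–2017, and linked to the later diagnosis. A man whose only earlier test was before 2009 or at a non-participating provider is in the 336 but cannot be a case.

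The same section handles the cohort differently for Secondary Aim 2. There it starts from the 40,000 men in the negative cohort (40,000 × 0.80 × 0.25 = 8,000 repeat testers). The primary aim uses the same cohort for incidence but does not start from it.

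At stake is the only quantified power statement for the primary aim. If it is too favourable, readers will expect a 20% year-on-year fall to be detected more often than the cohort can deliver.

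**Working it through.** **Inputs.** From Sample size: 420 diagnoses a year, 80% with testing history, hazard ratio 0.80, stated power 80%. From Data analyses: "For this analysis and all others, statistical significance will be set at" p < 0.05. Sidedness and the power formula are not stated, so two-sided 0.05 (z = 1.960), equal person-time in the two periods and independent Poisson counts are assumed. The share f of the 336 that meets Outcome 2 is not in the document. It is treated as unknown and varied from 40% to 100%.

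**Formulas.** Let d = 336 × f be the qualifying cases in a year, and |ln 0.80| = 0.2231.

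- Wald test of the log rate ratio, with d cases in the first year and 0.8d in the next: power = Φ(0.2231 / √(1/d + 1/(0.8d)) − 1.960).
- Schoenfeld, with d cases in each year (2d in total): power = Φ(0.2231 × √(2d/4) − 1.960).

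**Reproducing the stated figure (f = 100%).** 420 × 0.80 = 336.

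- Wald: √(1/336 + 1/268.8) = 0.0818; 0.2231/0.0818 = 2.727; Φ(0.767) = 77.8%.
- Schoenfeld: 0.2231 × √168 = 2.892; Φ(0.932) = 82.4%.

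These bracket the stated 80%, so the arithmetic is sound if 336 is the count per year. Reading 336 as the total for both years gives only 53.4%.

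**Half share (f = 50%, d = 168).**

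- Wald: √(1/168 + 1/134.4) = 0.1157; 0.2231/0.1157 = 1.928; Φ(−0.032) = 48.7%.
- Schoenfeld: 0.2231 × √84 = 2.045; Φ(0.085) = 53.4%.
- Detectable hazard ratio at 80% power, Schoenfeld: exp(−(1.960 + 0.842)/√84) = 0.737. The Wald form gives 0.716.

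**Over the range, year on year:**

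| Share of the 336 | Cases per year | Power at HR 0.80 (Wald to Schoenfeld) | HR detectable at 80% power |
|---|---|---|---|
| 100% | 336 | 77.8–82.4% | 0.79–0.81 |
| 90% | 302 | 73.5–78.3% | 0.78–0.80 |
| 75% | 252 | 65.6–70.7% | 0.76–0.78 |
| 50% | 168 | 48.7–53.4% | 0.72–0.74 |
| 40% | 134 | 40.7–44.8% | 0.68–0.71 |

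The 40% row corresponds to half coverage with 80% of those men having an earlier negative test in the network (0.5 × 0.8 = 0.40).

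**Which year carries the count.** If 336 × f is the lower, later year, the earlier year has 336 × f / 0.8. Wald power is then 86.2% at a full share (420 against 336) and 57.8% at half (210 against 168). On this placement, 80% power needs (1 + 0.8)/d = (0.2231/2.802)² = 0.00634, so d ≈ 284, a share of about 84%.

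**Two three-year periods at HR 0.80.** With three times the annual cases in the first period:

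- 50% share, 3 × 168 = 504 cases: Wald 91.6%, Schoenfeld 94.3%.
- 40% share, 3 × 134.4 = 403 cases: Wald 84.8%, Schoenfeld 88.7%.

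**The case against.** The strongest reply is that coverage of men is not coverage of diagnoses. The network aims to capture every diagnosis in both states. Its sites qualify on criteria such as at least five HIV diagnoses or at least 50 gay or bisexual men a year, 39 of the 59 health services are sexual health clinics, and 40,000 is a minimum. Diagnoses may well be concentrated there, so the qualifying share could be well above half. This stands as a reason not to fix the share at 50%. It does not rescue the 336. Capturing a diagnosis does not capture the man's earlier negative test or his person-time, and the laboratories are chosen for confirmatory and viral load testing. The share could also fall below half, because testing history carries no network or date limit.

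The second reply is that the annual comparison is not the primary analysis. Data analyses describes a multi-year random-effects Poisson model, and Sample size says pooling adds power. This also stands, and the three-year figures support it. The document still gives no power figure for that analysis.

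Third, if the 336 belongs to the later of two years, 80% power survives down to a share of about 84%. That is fair, but the article neither says so nor shows that the share is that high.

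A reader might go further and infer that taking 336 at face value gives the covered half of the population four times the incidence of the rest (336 against 84). The document does not support this. The 84 are diagnosed men without testing history, not cases in the uncovered half, and the Discussion already concedes that the cohorts are unlikely to be fully representative. Nor is scarce look-back in the first study years a valid objection to this figure, because the 420 is set for 2015–2017.

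**Conclusion.** The power statement is wrong as written: the event count is not the one that Outcome 2 delivers. The multiplication is correct, and 336 cases a year do give about 80% power. The fault is an unstated assumption that every diagnosed man with any testing history has a qualifying negative test in the cohort.

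The direction is certain and the size is open. Over shares of 40% to 90%, year-on-year power for a hazard ratio of 0.80 runs from about 41% to 78%, on two-sided 0.05 and equal person-time. A reader might infer that the true power is about 50%. That follows only if half of the men yield half of the qualifying cases, which the document does not say.

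A reader might also infer that the primary aim is underpowered. The document does not support that either: a contrast of two three-year periods keeps about 85–94% power at shares of 40–50%. That is a simple unadjusted contrast, however, and does not stand in for the power of the planned viraemia model. The point should be fixed, but it does not undermine the study.

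**What to change.** 1. Multiply 336 by the share of diagnosed men expected to have a linked negative test at a participating service or laboratory within the study window. The share can be counted now in the 50 existing sites. Failing that, show a range such as 40–90%.
2. Restate the annual cases and detectable hazard ratio, for example 168 cases and about 0.72–0.74 if the share is half. State the sidedness and the formula.
3. Give power for the three-year-period comparison or the multi-year viraemia model that will be run, in place of the unquantified remark that pooling has greater power.

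The cost is a count in data already held, some rewording, and a less favourable year-on-year figure. The design, outcome definitions and data collection do not change.
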